### Allocation and Blinding

This study will recruit an equal number of patients with gastric cancer and their spouses. Participants from Jingjiang People’s Hospital will be assigned to the experimental group, while participants from Taizhou People’s Hospital will be assigned to the control group. As the study involves a face-to-face psychological intervention, participants and personnel will be unblinded, but the outcome assessment will be blinded. Participant data will be anonymized using individual participant codes, and the database will not contain participant identifiers (eg, birth dates and case numbers).

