**Methods:**

This is a quasiexperimental study with a nonequivalent (pretest-posttest) control group design. The study will be conducted at 2 tertiary hospitals in Taizhou City, Jiangsu Province, China. A total of 42 patients with gastric cancer undergoing chemotherapy and their spouses will be recruited from each hospital. Participants from Jingjiang People’s Hospital will be assigned to an experimental group, while participants from Taizhou People’s Hospital will be assigned to a control group. The participants in the experimental group will be involved in 4 phases of the marital self-disclosure (different topics, face-to-face) intervention. Patients will be evaluated at baseline after a diagnosis of gastric cancer and reassessed 2 to 4 months after baseline. The primary outcome is the score of the Fear of Progression Questionnaire-Short Form (FoP-Q-SF) for patients. The secondary outcomes are the scores of the FoP-Q-SF for partners and the Dyadic Coping Inventory.

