#### Fear of Cancer Recurrence for Patients

The FoP-Q-SF is a 1-dimensional scale based on the Fear of Progression Questionnaire (FoP-Q). The FoP-Q-SF for patients includes 12 items, which are rated on a 5-point Likert scale (1 point indicating “never” and 5 points indicating “always”), with a total score ranging from 12 to 60 and with higher scores indicating higher fear of disease progression [40]. Wu et al [41] translated the scale into Chinese and tested its reliability and validity. The authors found that the Cronbach α coefficient of the total scale was 0.886 and the Guttman split-half coefficient was 0.855. Moreover, the Cronbach α coefficients of the 2 extracted common factors were 0.836 and 0.804, respectively, and the Guttman split-half coefficients were 0.806 and 0.828, respectively, which indicated good content consistency and met the requirements of psychometrics.

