### Outcome Assessment

Permission to adopt the 3 questionnaires has been obtained from the original researchers. A trained researcher will assess the outcomes, including sociodemographic variables and psychosocial variables. The sociodemographic variables include demographic and clinical characteristics. The psychosocial variables include fear of cancer recurrence for patients, fear of cancer recurrence for partners, and dyadic coping ability. The psychosocial variables will be repeatedly collected at 3 time points: baseline, after the second session of the intervention (nearly 2 months after baseline), and after the last intervention (almost 4 months after baseline). The control group will be reassessed at the same intervals. Furthermore, participants in the experimental group will be assessed to determine their experiences with the intervention after the last intervention session (Table 3). The conceptual framework is shown in Figure 2.

**Table 3 table3:** Study measures.

Variable	Outcome (measure)	Time point		
		Baseline	2 months after baseline (after the second intervention)	4 months after baseline (after the fourth intervention)
Inclusion criteria	Sociodemographic and clinical information	Yes	No	No
Primary outcome	FoP-Q-SF^a^ for patients	Yes	Yes	Yes
Secondary outcome	FoP-Q-SF for partners and Dyadic Coping Inventory	Yes	Yes	Yes
Intervention experience	In-depth interview	No	No	Yes

^a^FoP-Q-SF: Fear of Progression Questionnaire-Short Form.

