### Data Collection and Compensation

Upon agreeing to participate in the study, participants will be required to complete a paper-based baseline survey questionnaire. Participants in the intervention group will have the option to receive the marital self-disclosure intervention directly after completing the survey, while participants in the control group will only receive routine care. Both groups of participants will be tracked for a duration of 16 weeks after recruitment, and data will be collected at 3 time points: baseline and 2 and 4 months postintervention.

To ensure participant confidentiality, information collection will be restricted to face-to-face communication and a paper-based questionnaire. Birth dates or participant addresses will not be collected. All data will be stored on secure internal platforms of Hospitals A and B. At the end of the study period, only researchers will have access to the data set.

At each time point, the research team will contact participants via phone or WeChat, according to their preferences. Participants will be notified of upcoming follow-up studies and will be assisted in completing subsequent survey questionnaires. Upon completing each survey, they will receive small gifts, such as a hand sanitizer. Recruitment is expected to last for 12 months, with an additional 16 weeks needed for follow-up with all recruited participants to complete data collection. Data analysis will commence at the end of recruitment.

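### Outcome assessment is called blinded, but all primary and secondary outcomes are self-rated by patients and spouses whom the protocol calls unblinded

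*Protocol article*

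**What the plan says.** On blinding, the Allocation and Blinding section states that "participants and personnel will be unblinded, but the outcome assessment will be blinded". The same section fixes the group by site: "Participants from Jingjiang People’s Hospital will be assigned to the experimental group", while "participants from Taizhou People’s Hospital will be assigned to the control group". It then describes coding of participant data, which it presents as anonymization.

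On outcomes, the abstract's Methods paragraph says: "The primary outcome is the score of the Fear of Progression Questionnaire-Short Form (FoP-Q-SF) for patients". It continues: "The secondary outcomes are the scores of the FoP-Q-SF for partners and the Dyadic Coping Inventory". The instrument sections describe all three as Likert questionnaires. For the primary outcome, "The FoP-Q-SF for patients includes 12 items, which are rated on a 5-point Likert scale", giving a total from 12 to 60.

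On collection, the Outcome Assessment section says: "A trained researcher will assess the outcomes, including sociodemographic variables and psychosocial variables". Data Collection and Compensation describes paper questionnaires that the participants complete, and adds for follow-up: "Participants will be notified of upcoming follow-up studies and will be assisted in completing subsequent survey questionnaires".

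**The concern.** The blinding statement gives the trial a protection that its own description of the outcomes rules out. In a self-rated measure the respondent is the assessor. A patient who has been through the disclosure sessions knows it when answering items about fear of progression, and so does the spouse.

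Two things are at stake. A reader who takes the sentence at face value would rate the risk of detection bias as low for the primary outcome, when the design leaves it open. And any tendency of experimental couples to report less fear because they know they received the intervention, apart from a real change in fear, would appear in the results as an intervention effect. The Limitations section covers attrition, missing data and restriction to patients on chemotherapy, but does not mention unblinded self-report.

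**Working it through.** No figure in the document tests this point, so the check sets the sections side by side.

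1. **Who produces each score?** The patient FoP-Q-SF has 12 items on the patient's own fear. The partner version has 12 items on the spouse's own fear. The DCI has 37 items on coping within the couple. Each is answered on a 5-point scale, and Data Collection and Compensation has the participants complete the surveys. Respondents therefore generate every primary and secondary score. The in-depth interview in Table 3 is the one measure that is not a questionnaire; it concerns experience of the intervention, is confined to the experimental group, and is neither a primary nor a secondary outcome.

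2. **Do these people know the group?** Yes. The sentence that declares outcome assessment blinded also says that participants are not.

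3. **Would staff at the questionnaire know the group?** Group and hospital coincide (Methodology and Design; Allocation and Blinding), so anyone helping on site knows the allocation from the location alone. The 4-month interview, held only in the experimental group, is a further cue. Outcome Assessment names a trained researcher but does not say that this person is unaware of hospital or group.

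4. **Do the participant codes supply the blinding?** They remove identifiers. The text does not say that they conceal hospital or group.

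5. **Could blinding at a later step protect the scores?** Write b_E and b_C for the average shift in reported score that comes from knowing one's group, in the experimental and control groups, and δ for the true effect. Leaving aside other differences between the hospitals, the expected difference between groups at follow-up is

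   δ + (b_E − b_C).

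   Adding up Likert items needs no judgement, so masking whoever adds or enters them leaves b_E − b_C unchanged. Comparison with baseline does not remove it either, if the shift arises only after sessions have begun. The group-by-time comparison in the planned repeated-measures ANOVA would then carry it.

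6. **Can b_E − b_C be sized?** No. The document gives no estimate of either shift, and the Sample Size section does not state the SD it uses.

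**The case against.** The strongest defence is that the sentence is open about participants and personnel, and that the blinded part may refer to a separate assessor, scorer or data handler. The article does name a trained researcher for assessment and does describe coding. A condensed article need not set out its masking procedure, and participants cannot be blinded to a face-to-face psychological intervention.

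Part of this stands. Blinded scoring, data entry or analysis is not ruled out, so a reader should not infer that no blinding of any kind exists. Self-report is also a reasonable way to measure fear; the fault lies in the label. But the defence does not rescue the label, because blinding at those later steps does not protect self-rated scores. Nor is this a matter of missing detail, since the article asserts a property that its own outcome descriptions contradict.

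Three stronger readings are tempting and not supported:

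- **That session nurses help fill in the questionnaires, or that follow-up takes place in their presence.** The text does not say who assists or what the help consists of. It gives delivery to two communication-led nurses and assessment to a trained researcher. Follow-up is placed after the second and last sessions, with no interval from session to questionnaire.
- **That the bias is known to favour the intervention.** This is a plausible inference, and *could* is as far as it goes.
- **That the bias is a known share of the planned effect.** An assumed shift of 1 or 2 points would be 1/2.88 = 35% or 2/2.88 = 69% of 2.88 points. But the shift is invented, and 2.88 is reported from an earlier breast cancer study without being expressly adopted as this trial's target difference.

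**Conclusion.** The point holds in a limited form. As written, the claim of blinded outcome assessment is wrong for the primary outcome and for both secondary outcomes, because unblinded respondents produce the scores. Staff present at the hospital would also know the group. Any blinding that does exist further down the line cannot remove bias that enters when participants answer.

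That bias could favour the intervention; neither its direction nor its size is established by the document. The conclusion rests on the article's own statements about who is unblinded, what the outcomes are, who completes them and how hospitals map to groups. It needs no assumption about which staff member assists. The correction should be made, because it changes how the primary result may be read and costs little.

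**What to change.** 1. **Allocation and Blinding.** Replace the claim with wording such as: *The primary and secondary outcomes are self-reported by patients and spouses who know their group, and are therefore not blinded.* Add a statement about blinded data entry or analysis only if group and hospital are actually concealed at that step. The current text does not show that they are, so this should not be asserted by default.

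2. **Data Collection and Compensation.** Specify that participants complete the questionnaires themselves. State that any help is given in the same way at both hospitals, by the trained researcher already planned and not by staff who deliver the sessions. This does not restore blinding, since the hospital still reveals the group; it keeps the help uniform and separate from delivery. Where follow-up questionnaires have already been collected, report who helped and how.

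3. **Limitations.** Add unblinded self-report of all primary and secondary outcomes.

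The cost is minor wording changes and a less favourable rating for risk of bias. No extra staff are needed. The change does not remove self-report bias; it stops the article from claiming a protection that the design cannot give.

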### Data Analysis

Statistical analysis will be conducted using IBM SPSS 21.0 (IBM Corp). The level of statistical significance will be set as α=.05. Descriptive statistics will be used to describe the sociodemographic and psychosocial variables, including percentages, means, and standard deviations. For comparing the baseline characteristics of the 2 groups, the Student *t* test or Mann-Whitney *U* test will be used for quantitative variables and the chi-square test will be used for categorical variables. Two-way repeated-measures ANOVA will be performed to determine the presence of a significant change in the fear of cancer recurrence and DCI in the intervention and control groups in order to analyze the effects of the intervention and compare the control group with the experimental group at baseline and 2 and 4 months postintervention. This analysis will be performed on an intention-to-treat basis. A *P*-value of <.05 will be considered statistically significant for differences between the 2 groups.

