### Sample Size

The sample size will be calculated using the following formula for sample size based on the study by Charan and Biswas [33]: sample size = 2 (SD) 2 × (Zα/2 + Zβ)2 / D2. It is based on the FoP-Q-SF (primary outcome) from a previously published study [15]. It showed a 95% power to detect a mean difference of 2.88 points between the control and experimental intervention groups in 61 Chinese patients with breast cancer. Statistical significance will be calculated to achieve a statistical power of 0.9 at a 5% significance level for 70 participants in each group. A 2-tailed test will be used to test the hypothesis. The sample size of each dependent variable is 35. To address dropout, an additional 20% is added to the calculation. As a result, the sample size for the experimental and control groups is 42. Consecutive sampling will be used in this study.

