### Limitations

This study has some minor limitations. First, this study involves a long-term intervention, and some participants may not complete the study owing to loss of follow-up or physical deterioration during treatment. Second, missing data may influence the results and must be addressed statistically. To overcome this bias, a 20% attrition rate will be included in the sample size calculation, and an intention-to-treat analysis will be performed during the data analysis. Finally, this study will only include patients during chemotherapy.

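### The repeated-measures ANOVA is labelled intention-to-treat but, as specified, analyses completers only, and the 20% sample-size allowance does not correct attrition bias

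*Protocol article*

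**What the plan says.** The Data Analysis section names SPSS 21.0 and one inferential method for the outcomes: "Two-way repeated-measures ANOVA will be performed to determine the presence of a significant change in the fear of cancer recurrence and DCI". The method covers baseline, 2 months and 4 months in both groups. The section then adds: "This analysis will be performed on an intention-to-treat basis". It names no imputation and no likelihood-based model.

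The Limitations section accepts that some participants may be lost to follow-up or deteriorate physically, and that missing data have to be dealt with statistically. Its answer is: "To overcome this bias, a 20% attrition rate will be included in the sample size calculation, and an intention-to-treat analysis will be performed".

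The Sample Size section adds 20% to 35 per group and arrives at 42.

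**The concern.** Two statements do not fit together. A classical repeated-measures ANOVA needs a complete row for each subject. A patient who misses the 2-month or 4-month questionnaire drops out entirely, and the scores already collected go too. An analysis restricted in this way is not intention-to-treat in the usual sense, whatever its label.

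The Limitations sentence also credits a larger sample with removing bias. Recruiting more couples replaces lost numbers. It does not change who is lost.

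The protocol gives reasons to expect losses related to the outcome. The Introduction says that adverse reactions make patients more fearful of recurrence and progression, and Limitations names deterioration as a cause of loss. Losses may also differ by arm, because only the experimental couples have four sessions of 45 to 70 minutes plus weekly homework. If the more fearful patients leave one arm, the completers' comparison can show an effect that is not there, or hide one that is.

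**Working it through.** **The plan's own figure.** 35 × 1.20 = 42, as stated. With 20% loss, 42 × 0.80 = 33.6 completers per group remain, slightly short of 35 (35 / 0.80 = 43.75, so 44 would be needed). The allowance therefore roughly restores the number analysed.

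**How many rows the ANOVA loses.** If each follow-up visit is missed independently by 10%, 0.90² = 81% have complete data (34 of 42). At 15% this is 72% (30 of 42), and at 20% it is 64% (27 of 42).

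**Inputs for the bias illustration**
- Planning difference: 2.88 points (Sample Size).
- SD: not stated; the formula "sample size = 2 (SD) 2 × (Zα/2 + Zβ)2 / D2" carries only the symbol. Assumed 7.8, from the two dimension SDs in the Introduction taken as uncorrelated: √(4.52² + 6.34²) = √60.63 = 7.79.
- Correlations between visits (r12, r13, r23): assumed, between 0.36 and 0.7.
- Loss of the 4-month score: 20% per arm, assumed random in control. In the experimental arm the log-odds of loss rise by 1 per SD of either the 2-month score or the change from baseline to 2 months.
- No true effect.

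**Formulas.** With this mechanism, experimental completers have a mean on the driving variable about 0.174 SD too low (found numerically), so δ = -0.174 × 7.8 = -1.36. Under normality the bias in the completers' group difference in change is:
- loss driven by the 2-month score: δ(1 - r12) at 2 months, δ(r23 - r12) at 4 months;
- loss driven by the 2-month change: δ√(2(1 - r12)) at 2 months, δ(1 - r12 - r13 + r23) / √(2(1 - r12)) at 4 months.

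| r12 / r13 / r23 | Score-driven: 2 mo | 4 mo | Change-driven: 2 mo | 4 mo |
|---|---|---|---|---|
| 0.5 / 0.5 / 0.5 | -0.68 | 0 | -1.36 | -0.68 |
| 0.6 / 0.6 / 0.6 | -0.54 | 0 | -1.22 | -0.61 |
| 0.6 / 0.36 / 0.6 | -0.54 | 0 | -1.22 | -0.97 |
| 0.5 / 0.4 / 0.7 | -0.68 | -0.27 | -1.36 | -1.09 |

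A simulation of 1,000,000 subjects agreed with these values to within about 0.02. Setting all three correlations to 0.7 or to 0.36 moves the ends at 2 months slightly, to -0.4 and -1.5. In the same runs a likelihood-type estimate of the 4-month change, using every observed score, was off by no more than about 0.02. At 2 months nobody in this scenario is missing, so using all scores gives no bias.

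**Does a larger sample help?** The formulas contain no n. A separate simulation (SD 7.8, all correlations 0.6, log-odds 1.2 per SD of change) gave a completers' bias at 4 months of -0.73, -0.73, -0.68, -0.70 and -0.69 for n = 35, 42, 44, 84 and 420 per group. The false-positive rate was about 7% at n = 35 to 44 and 24% at n = 420: a larger sample makes the same bias easier to declare significant.

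**The case against.** The document is a condensed article. It says that missing data must be addressed statistically, and the choice of method is commonly left to an analysis plan. It names SPSS but no procedure, so complete-row deletion is a property of the classical method and not a rule the text states. Imputing before the ANOVA would honour the intention-to-treat label. All of this stands. A reader might infer that an intention-to-treat analysis cannot be delivered at all, and the document does not support that. What remains is that the article does fix a method, fixes an analysis basis that this method alone does not meet, and makes a claim about the 20% allowance that is wrong as stated.

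Three other readings go too far.
- A reader might take the whole 20% to be deterioration. Limitations names loss to follow-up or deterioration and gives no split, and the Sample Size section presents the 20% as a general dropout allowance.
- A reader might compare raw 4-month means. With score-driven loss and correlation 0.6, completers would show -2.88 - 0.82 = -3.70 for a true -2.88. The same shift of -1.36 × 0.6 = -0.82 is already there at baseline, so it does not measure bias in the treatment effect. The change contrasts above do.
- A reader might take the figures as a forecast. When loss was random in both arms, or followed the same rule in both, the simulated bias was about 0.

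**Conclusion.** The point holds for the analysis as specified: a completers' analysis under an intention-to-treat label, and a sample-size allowance presented as a cure for bias. Under the stated assumptions the completers' difference in change is off by about -0.5 to -1.4 points at 2 months and 0 to -1.1 at 4 months. The largest values are 1.36 / 2.88 = 47% and 1.09 / 2.88 = 38% of the planning difference. The negative sign favours the intervention only because the more fearful experimental patients were assumed to leave; the opposite pattern would reverse it. The SD, the correlations and the one-sided dropout mechanism are assumptions, so the figures show what is possible and do not predict this trial's bias. At the planned size the inflation of the false-positive rate in the simulated case is modest. The change should be made, because a better method is available in the same software.

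**What to change.** 1. In Data Analysis, replace the ANOVA with a linear mixed model for repeated measures (SPSS MIXED, REML, unstructured covariance). Enter the baseline, 2-month and 4-month scores all as outcomes, with group, time and group × time as fixed effects. Every enrolled participant with any score is then included, also those lost before month 2, and the group × time contrasts give the effect. Keeping baseline as an outcome also avoids fixing a baseline adjustment, which is debatable when the groups are two non-randomised hospitals.
2. Add a delta-adjusted sensitivity analysis: shift the imputed scores of those lost to deterioration by a range of prespecified amounts and report how far the result moves.
3. In Limitations, say that the 20% allowance protects precision, and delete the claim that it overcomes bias.

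Cost: wording and slightly more analysis work; same software, no new visits. The main model still assumes that losses depend only on observed scores, which is why the second item is needed.
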